## 3.6 Sample size calculations

Based on a preliminary review of descriptive statistics in both countries, we anticipate the following numbers:

- Scotland:
  - ChAdOx1:
  - BNT162b2:
- Brazil
  - ChAdOx1: 10 million individuals with booster from 49M with 2 doses
  - BNT162b2: 5 million individuals with booster from 28M with 2 doses

If adequate numbers are not available for statistical analysis for a specific vaccine, we will not progress that analysis and censor individuals who receive that vaccine.

# Data and Data Validation

## 4.1 Data variables available

Tables 1 and 2 lists the groupings of variables available for this study by data source. Exposure data are described in the vaccinations category. Outcome data are described in the secondary care, mortality and laboratory tests categories. The rest of categories contain data on potential confounding factors and effect modifiers.

**Table 1: Data items/variables and data sources**

| **Data category** | **Data item** | **Data source** |
| --- | --- | --- |
| Demographic | Sex | GP |
|  | Age | GP |
| Socioeconomic | SIMD | GP |
| Other characteristics | Body Mass Index (BMI) | GP |
|  | Smoking | GP |
|  | Blood Pressure | GP |
| Geographic | Urban Rural Index (UR6); Health Board | GP |
| Clinical diagnoses | Underlying conditions  (e.g., asthma, cardiac disease, immunosuppression etc.) | GP |
| Vaccinations | Vaccine type | GP, TVMT |
|  | Vaccine dose | GP, TVMT |
|  | Vaccination date | GP, TVMT |
| Laboratory tests | RT-PCR positive SARS-CoV-2 | ECOSS |
|  | RT-PCR negative SARS-CoV-2 | ECOSS |
|  | Date of RT-PCR test | ECOSS |
| Genomic Vigilance | Date of prevalence of variants | GISAID |
| Secondary care | Hospital admissions | RAPID/SMR |
| Mortality | Death with COVID-19 as the main cause according to death certificate, or death within 28 days of a positive RT-PCR test for COVID-19 | NRS |
| Abbreviations: Scottish Index of Multiple Deprivation (SIMD), Body Mass Index (BMI), Electronic Communication of Surveillance in Scotland (ECOSS), Reverse-transcription polymerase chain reaction (RT-PCR); Turas Vaccination Management Tool (TVMT); Scottish Morbidity Record (SMR); National Records of Scotland (NRS) | | |

**Table 2: Data items/variables and data sources in Brazil**

| **Data category** | **Data item** | **Data source** |
| --- | --- | --- |
| Sociodemographic | Sex | SI-PNI |
|  | Age | SI-PNI |
|  | Municipality-level IBP | SI-PNI |
|  | Education | (SIVEP-Gripe) |
|  | Race | SI-PNI, eSUS, SIVEP-Gripe |
|  | City |  |
| Clinical diagnoses | Underlying conditions  (Cardiac disease, chronic kidney disease, etc) | eSUS, SIVEP-Gripe |
| Vaccinations | Vaccine type | SI-PNI |
|  | Vaccine dose | SI-PNI |
|  | Vaccination date | SI-PNI |
|  | The primary reason for vaccination: 2 categories (comorbidities/other) | SI-PNI |
| Genomic Vigilance | Date of prevalence of variants | GISAID |
| Laboratory tests | Date of RT-PCR/rapid antigen test | eSUS |
|  | RT-PCR/rapid antigen positive SARS-CoV-2 | eSUS |
|  | RT-PCR/rapid antigen negative SARS-CoV-2 | eSUS |
| Secondary care  Mortality | COVID-19 hospital admission date | SIVEP-Gripe |
|  | COVID-19 death | SIVEP-Gripe/eSUS |
|  | COVID-19 death date | SIVEP-Gripe/eSUS |

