## 3.4 Data sources

In Scotland, we will draw on the following databases:

- Primary care data: General Practices (n=940) for information on demographics, other population characteristics and vaccination data.
- Vaccination data: Vaccines administered in national vaccination centres and data available via the Turas Vaccination Management Tool (TVMT).
- Secondary care data: Hospital admissions through the Scottish Morbidity Record (SMR) and Rapid Preliminary Inpatient Data (RAPID).
- Laboratory test data: RT-PCR laboratory confirmed SARS-CoV-2 infection and data available via the Electronic Communication of Surveillance in Scotland (ECOSS) database.
- Mortality data from National Records Scotland (NRS)

Equivalent datasets will be used for other UK/international countries. In Brazil, we will analyse deterministically linked data provided by the Ministry of Health:

- COVID-19 vaccination (SI-PNI): Dates and types of vaccination administered, primary reason for vaccination, indigenous status, pregnancy status.
- Acute Respiratory Infection Suspected Cases (eSUS-Notifica): register of suspected and confirmed COVID-19 cases
- Severe Acute Respiratory Infection/Illness (SIVEP-Gripe): contains all hospitalisations and deaths due to severe acute respiratory illnesses, including COVID-19.

The above three databases all have whole population coverage, with returns from both public and private healthcare systems. However, data quality may vary geographically (typically data quality is better in the south of Brazil). Testing capacity has also improved over the course of the pandemic, but most improvements occurred prior to the vaccination programmes starting. In addition to the above datasets, it may be possible in the future to obtain linkage to general hospital records for patients treated within the public healthcare system (covering approximately 70% of hospitalisations in Brazil).

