### 5.1.3 Potential confounders

We will consider adjusting for age, sex, socioeconomic position, geography and where possible, comorbidities. More specifically, we anticipate adjusting for the following confounders in Scotland: age (five-year bands^^[[3]](#footnote-2)^^), sex, socioeconomic position (SEP) measured by quintiles of the Scottish Index of Multiple Deprivation (SIMD) (1 refers to most deprived and 5 refers to least deprived), residential settlement measured by the urban/rural 6 fold classification (1 refers to large urban areas and 6 refers to small remote rural areas), household size, number and types of comorbidities commonly associated with COVID-19 illness (asthma, chronic kidney disease, liver cirrhosis, chronic neurological condition, heart failure, diabetes (type 1 and type 2), dementia, coronary heart disease), risk factors (smoking status, blood pressure, body mass index (BMI)) and Health Board.

In Brazil, we anticipate adjusting for age (five-year bands), sex, the primary reason for vaccination, race/ethnicity and calendar week will be accounted for within the statistical models.

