### 5.1.5 Analytical techniques

We will commence analysis by conducting descriptive analyses to visually inspect trends in vaccination delivery, age-specific COVID-19 hospitalisations and COVID-19 deaths, including by age group and sex. This will include checking the number of people who have received two doses and the length of follow-up available following the second dose by vaccine type. Including plotting Lexis diagram to afford for the correlated structure of the data (Calendar Time/Length of Follow-up)

For the analysis consisting of individuals with at least two doses, we will stratify the cohort based on the month of the second dose of each individual. The vaccination status will be classified as:

- Second dose:
  - <2 weeks
  - 2-9 weeks
  - 10-19 weeks
  - ≥20 weeks without a booster dose [Reference Period]
- Booster dose:
  - <2 week
  - 2-4 weeks
  - 5-8 weeks
  - 9-12 weeks
  - ≥13 weeks

This variable will be used to fit a Poisson regression to obtain rate ratios (RRs) and their 95% confidence intervals (CIs). If we observe overdispersion, we will consider using Negative Binomial regression models or Poisson with robust standard errors. Models will be adjusted for the relevant confounders above, including a set of dummy variables for calendar week.

The models will be fit to a dataset with all events and a random sample, without replacement, of 100 individuals per event (for hospitalisation and death, 10 for positive tests). The sample weights will be calculated to represent the sampling fraction, thus ensuring the correct calculation of the person-years at risk for the whole population.

The primary analysis for the test negative will be on individuals who are symptomatic at the time of test and the date of symptom onset is 0-10 days before the test. We will then establish the number of weeks post-vaccination for the cases and controls calculated as time between sample collection date and vaccine dose. The odds' ratio will be calculated using a logistic regression. Adjusted for: race/ethnicity, comorbidities, dummy variables for calendar week, age (five-year bands), sex. Controls will be defined based on a negative test.

We will also construct a propensity score to be tested among those in the primary cohort and use this as an inverse propensity weight.

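### Brazil's cohort rate-ratio model captures risk group only through a two-level reason for vaccination, so residual confounding may bias the time-since-booster gradient in either direction

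*SAP*

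**What the plan says.** SAP Section 3.4 lists what SI-PNI supplies for Brazil: "Dates and types of vaccination administered, primary reason for vaccination, indigenous status, pregnancy status". Table 2 carries the reason forward at two levels ("The primary reason for vaccination: 2 categories (comorbidities/other") and has no row for pregnancy or indigenous status. Section 5.1.3 then gives the country-specific list: "In Brazil, we anticipate adjusting for age (five-year bands), sex, the primary reason for vaccination, race/ethnicity and calendar week". For Scotland the same section names eight comorbidities plus smoking, blood pressure and BMI.

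Table 2 does list underlying conditions for Brazil, but takes them only from eSUS and SIVEP-Gripe. Section 3.4 describes these as a register of suspected and confirmed cases and a register of severe respiratory hospitalisations and deaths.

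For the cohort analysis, Section 5.1.5 adds two controls on timing: "we will stratify the cohort based on the month of the second dose of each individual", and adjustment "including a set of dummy variables for calendar week". It also plans weighting: "We will also construct a propensity score to be tested among those in the primary cohort and use this as an inverse propensity weight". The covariates of that score are not listed. The test-negative model in the same section has its own covariate list, which includes comorbidities and not the reason for vaccination.

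**The concern.** Objectives 3 to 5 of Section 2.2 concern how the rate ratio changes with time since the booster's maximum effect, and Section 5.1.5 tests that change for trend. Anything that influences both how early a person was boosted and that person's risk of the outcome distorts this gradient directly.

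With two levels, everyone whose recorded reason is not a comorbidity is pooled as other. If that pool mixes groups that were boosted at different times and carry different risk at the same age, part of the gradient reflects who is in each band and not a change in protection. The full cohort has no ready substitute, because a cohort member who was never notified to eSUS or SIVEP-Gripe would have no comorbidity record there. Sample size does not help: in a cohort of millions a modest bias can be statistically clear.

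**Working it through.** The SAP gives no bias or precision figure on this point, so there is none to reproduce.

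**1. What the timing controls leave open.** For each boosted person, time since booster = calendar date − second-dose date − interval from second dose to booster. Hold the first two terms fixed, and time since booster and interval move one for one. The 2–4 week band ends where the 5–8 week band starts. So, for the same second-dose date and the same day, someone at 13 weeks or more was boosted over 13 − 5 = 8 weeks sooner after dose two than someone at 2–4 weeks. A month-wide stratum (31/7 = 4.4 weeks) and a one-week calendar dummy loosen this, but at least 8 − 4.4 − 1 = 2.6 weeks remain. The strata control the timing of the primary series. The contrast between booster bands is still one between people boosted sooner and people boosted later.

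**2. Room for selection.** From Section 3.6, the boosted share in Brazil is 10/49 = 20.4% (ChAdOx1), 5/28 = 17.9% (BNT162b2) and 15/77 = 19.5% together. Boosted people were a minority of the two-dose population, so selection into early boosting is plausible.

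**3. Possible size.** Let p1 and p0 be the shares of an unmeasured group in the late (≥13 weeks) and early (2–4 weeks) bands, within strata of the adjusted covariates. Let R be that group's rate ratio for the outcome. With no true waning, the late-to-early ratio is multiplied by

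(1 + p1(R − 1)) / (1 + p0(R − 1)).

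All three inputs are assumptions; none is in the SAP.

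| p1 | p0 | R | Factor |
| --- | --- | --- | --- |
| 15% | 5% | 2 | 1.15/1.05 = 1.10 |
| 30% | 3% | 3 | 1.60/1.06 = 1.51 |
| 15% | 10% | 1.5 | 1.075/1.05 = 1.02 |
| 30% | 10% | 2 | 1.30/1.10 = 1.18 |
| 15% | 10% | 0.5 | 0.925/0.95 = 0.97 |
| 50% | 10% | 0.5 | 0.75/0.95 = 0.79 |
| 10% | 10% | any | 1.00 |

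The first two rows are the extremes for p1 of 15–30%, p0 of 3–5% and R of 2–3. The last row is the case where existing adjustment already balances the group.

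**4. Whether a small factor would be visible.** Assume 1,000 events in each band (the SAP gives no event counts). The standard error of the log ratio is √(1/1000 + 1/1000) = 0.045. A factor of 1.15/1.05 has a log of 0.091, so z = 0.091/0.045 ≈ 2.0. Even the low end of the first range could register as a trend.

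**The case against.** The strongest case for the plan has four parts.

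- **The coding may not be the team's choice.** Section 4.1 presents Table 2 as the groupings of variables available. The two levels may be how the data arrived. A reader might infer that the team is throwing away finer priority-group data, but the SAP does not show that finer categories exist or that they decided booster order. This stands, and the remedy on categories has to be conditional. It does not touch pregnancy and indigenous status, which Section 3.4 names as SI-PNI fields.
- **Existing controls absorb part of the rollout order.** People prioritised early in the primary series will tend to share a second-dose month, and five-year age bands handle age priority. This stands in part: step 1 shows that selection into early boosting within a stratum remains. Section 4.2 constructs the interval between second dose and booster. However, given second-dose month and calendar week, it is nearly collinear with time since booster, so it cannot replace a risk-group covariate.
- **Other safeguards are planned.** Section 5.1.3 opens by considering comorbidity adjustment where possible, Section 5.1.4 stratifies by risk group when data allow, and Section 5.1.8 considers negative-control outcomes. All are conditional, and in Brazil the comorbidity data come from illness registers. The propensity score, if built from the Table 2 fields, inherits the two-level variable.
- **The direction is unknown.** A group boosted early for a non-medical reason could be at lower risk of severe disease, which would hide waning. This stands in full.

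**Conclusion.** The point holds as a residual-confounding weakness in Brazil's cohort Poisson model. The country-specific list has one two-level risk-group covariate and leaves out two fields that the SAP itself names, and the timing controls do not fully close the gap. The size cannot be computed from the SAP. It is 1.10 to 1.51 under the assumed shares of 15–30% and 3–5% with R of 2 to 3, below 1 if the early-boosted group is at lower risk, and 1.00 if existing adjustment balances the groups.

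A reader might go further and infer that the late booster bands are filled with higher-risk people, so that any waning found in Brazil would be spurious. The SAP does not support that: it gives neither the order in which groups were boosted nor the risk profile of any band. Nor does the point extend to the test-negative model, which adjusts for comorbidities and does not list the reason for vaccination.

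**What to change.** In both the cohort Poisson model and the propensity model for Brazil:

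- Add pregnancy and indigenous status from SI-PNI, after checking how far indigenous status overlaps with race/ethnicity, which is already adjusted for.
- Use the recorded reason-for-vaccination categories in place of the two levels, where the extract holds them and numbers allow. Merge only those too small to fit. If the extract holds only two levels, say so.
- State which dose record supplies these fields. It should be one that boosted and unboosted people both have.
- List the propensity-score covariates.
- Report the two-level version as a sensitivity analysis, so that readers can see how far the gradient moves.

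The cost is a few extra parameters in a cohort of millions, and possible missingness in these fields, to which the rule in Section 5.2 would apply.

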## 4.2 Constructed variables

1. Previous infection, if an individual had a previous RT-PCR/Antigen positive test more than 90 days before the event of interest. Only the first positive test before the current event will be considered. This variable will be created differently for the cohort and TND.
   1. TND: Individuals with a previous RT-PCR or Antigen test positive considering the current sample collection date. (No previously infected, 91-180 days, >180 days)
   2. Cohort: Individuals with a previous RT-PCR or Antigen test considering the study start date (2021/09/15). (No previously infected,28-90 days,91-180 days, >180 days)
2. Interval between second and booster dose

## 4.3 Consistency and error checking

We will check for patterns of missingness and implausible values (e.g. date of second vaccine dose being earlier than the first) for all analytical variables being used, with a record maintained of reasons for excluding any records from analysis. In the case where a variable of interest has high levels of missingness, we will consider using alternative variables that are closely related as a proxy for these missing data.

# Statistical Analyses

### 5.1.1 Exposures of interest

###

Our primary exposure will be receipt of a COVID-19 vaccine booster, with categories to include time since receipt of a booster dose. In this setting, a patient’s vaccination status (exposure) will change over time, as a time-varying exposure.

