# Introduction

This study aims to determine whether protection from COVID-19 vaccination wanes after the booster dose of SARS-CoV-2 vaccines. If possible, we plan to conduct harmonised analyses across different contexts to strengthen confidence that trends in variants (VOCs) do not drive findings, increase statistical power, and allow robustness of results when adjusting for differing confounders to be assessed. A current collaboration will enable analyses to be conducted in Scotland and Brazil.

In Scotland, the primary series (two doses) mainly included Oxford-AstraZeneca (ChAdOx1) or Pfizer-BioNTech (BNT162b2). The primary series in Brazil included: ChAdOx1, CoronaVac, BNT162b2 and Ad26.COV2.S. At present, the vaccination programme in Scotland uses two mRNA vaccines as boosters: Pfizer-BioNTech (BNT162b2) and Moderna (mRNA-1273) vaccines. The vaccination programme in Brazil currently offers mainly BNT162b2 as a booster dose of a primary series with BNT162b2, ChAdOx1, Ad26.COV2.S or CoronaVac. In this study we will analyse data of BNT162b2 and ChAdOx1 as a primary series and booster with BNT162b2.

We aim to evaluate the real-world impacts of being fully vaccinated and assess whether the rate of infection and severe outcomes (deaths and hospitalisations) (RR) diminishes over time after the booster dose. e will use deidentified individual-level linked data. All data and analyses will be hosted within secure analytical environments.

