## 3.5 Inclusion/exclusion criteria

Inclusion criteria for the primary cohort:

- Receive at least two doses of BNT162b2 or ChAdOx1 before or during the study period.

Exclusion criteria for the primary cohort:

- Inconsistent vaccination records (i.e. received a second dose with no record of a first dose, received doses from different vaccine types or interval between doses of less than 14 days)
- Missing essential covariates (sex, age, geography)
- Children (under the age of 18 years)
- Hospitalization previous to the study start date
- A positive test within 28 days of the study start date

Inclusion criteria for the TND:

- Receive at least two doses of BNT162b2 or ChAdOx1 at the sample collection date.

Exclusion criteria for the TND:

- Tests within 90 days of a previous positive test
- Negative tests followed by a positive test within 7 days
- Negative tests within 14 days of a previous negative test
- Missing essential covariates (sex, age, geography)
- Children (under the age of 18 years)

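### The restriction to BNT162b2 boosters is never made operational: no exposure, banding or eligibility rule delivers it, so other booster products could enter the boosted group

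*SAP*

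**What the plan says.** The Introduction sets the scope: "In this study we will analyse data of BNT162b2 and ChAdOx1 as a primary series and booster with BNT162b2". It also shows that other boosters will be in the data. For Scotland, "the vaccination programme in Scotland uses two mRNA vaccines as boosters: Pfizer-BioNTech (BNT162b2) and Moderna (mRNA-1273) vaccines". For Brazil the wording is weaker than exclusive use: "The vaccination programme in Brazil currently offers mainly BNT162b2 as a booster dose".

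The operational sections read as follows.

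- **Exposure (5.1.1):** "Our primary exposure will be receipt of a COVID-19 vaccine booster, with categories to include time since receipt of a booster dose".
- **Status variable (5.1.5):** one booster group, divided only by weeks since the dose, the last band being 13 weeks or more.
- **TND inclusion (3.5):** "Receive at least two doses of BNT162b2 or ChAdOx1 at the sample collection date". The TND exclusions contain no rule on mixed products.
- **Cohort inclusion (3.5):** "Receive at least two doses of BNT162b2 or ChAdOx1 before or during the study period". Among the records excluded as inconsistent are those of people who "received doses from different vaccine types or interval between doses of less than 14 days".
- **Population (3.3):** for Brazil, boosted adults whatever vaccine they had as primary series.
- **Numbers (3.6):** if a vaccine has too few recipients, "we will not progress that analysis and censor individuals who receive that vaccine".
- **Objectives and strata (2.2, 5.1.4):** the objectives are to be met by vaccine type, without saying whether that is the primary or the booster vaccine. The one vaccine stratum listed is the primary schedule; further stratification by vaccine type is left open.

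**The concern.** The primary exposure cannot be coded to the stated scope from the rules as written. An analyst must either add an unwritten restriction or depart from a written one, and the Scottish and Brazilian teams could do so differently.

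The main aim (2.1) is the change in risk with time since the booster's maximum effect. If other products are counted as boosted, each time band's estimate is an average over products. If the mix differs between bands, for instance because supply changed during the roll-out, a difference between products can show up as waning or conceal it. Country estimates could also differ because the product mix differs.

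**Working it through.** The SAP gives no figure to reproduce here, so the check is to apply each rule to the people it would meet.

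**Step 1: TND.** Take a person with two BNT162b2 or two ChAdOx1 doses, then mRNA-1273, tested later.
- The inclusion rule is met.
- No exclusion concerns the booster product.
- 5.1.1 and 5.1.5 class the person as boosted.
- The censoring rule in 3.6 acts only on a vaccine with too few recipients.

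So this person is out of scope by the Introduction but boosted by the written rules.

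**Step 2: cohort.** The mixed-product exclusion does not say whether the booster counts as a dose.

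| Regimen | Scope (Introduction) | Booster counts as a dose | First two doses only |
|---|---|---|---|
| BNT162b2 ×2, then BNT162b2 | in | kept | kept |
| ChAdOx1 ×2, then BNT162b2 | in | **removed** | kept |
| ChAdOx1 ×2, then ChAdOx1 | out | **kept** | **kept** |
| BNT162b2 or ChAdOx1 ×2, then mRNA-1273 | out | removed | **kept** |

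Bold cells depart from the scope, and each reading has some. The first reading also excludes people because of a booster received during follow-up, which discards their earlier unboosted time.

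Section 3.6 shows what the first reading would cost. Brazil expects 10 million boosted people with a ChAdOx1 primary series and 5 million with BNT162b2. The ChAdOx1 group is 10 / (10 + 5) = 67% of the boosted, and all of it except any third ChAdOx1 doses would go. The first reading is therefore unlikely to be intended, which leaves the reading that admits every product.

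**Step 3: population.** Section 3.3 admits any primary vaccine in Brazil. The inclusion rules in 3.5 narrow this to two products, but 3.3 and the Introduction still disagree.

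**Step 4: possible size, on assumed values only.** The SAP gives neither booster product shares nor product-specific effects. Let s be the share of boosted person-time on another product, with a common reference group and no other differences:

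pooled RR = (1 − s) × RR(BNT162b2) + s × RR(other)

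Assume RR(BNT162b2) = 0.30.

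| s | RR(other) = 0.20 | RR(other) = 0.30 | RR(other) = 0.40 |
|---|---|---|---|
| 10% | 0.27 + 0.02 = 0.29 | 0.30 | 0.27 + 0.04 = 0.31 |
| 30% | 0.21 + 0.06 = 0.27 | 0.30 | 0.21 + 0.12 = 0.33 |
| 50% | 0.15 + 0.10 = 0.25 | 0.30 | 0.15 + 0.20 = 0.35 |

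Now hold both product effects constant over time and let s fall from 40% at 2–4 weeks to 10% at 13 weeks or more.
- RR(other) = 0.20: 0.18 + 0.08 = 0.26 becomes 0.29, ratio 0.29 / 0.26 = 1.12, which looks like waning.
- RR(other) = 0.40: 0.18 + 0.16 = 0.34 becomes 0.31, ratio 0.31 / 0.34 = 0.91, which would hide some true waning.
- RR(other) = 0.30: no change.

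**The case against.** The strongest reply is that the Introduction governs. It states what will be analysed, so booster in later sections may be shorthand for the BNT162b2 booster. The objectives are set by vaccine type, and 3.6 speaks of analyses for a specific vaccine, neither of which suggests an intention to mix products. In the cohort, the literal mixed-product exclusion would remove mRNA-1273 recipients altogether.

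Much of this stands. A reader might infer that the plan pools mRNA-1273 and other boosters into the BNT162b2 estimates. The SAP does not say so; it is silent on how those recipients are handled. Nor can it be said of the cohort, without qualification, that eligibility admits any booster product: that holds only if the mixed-product rule is confined to the primary series.

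The reply does not close the gap. A scope sentence does not say whether a person with another booster is excluded, censored at that dose or put in a separate category, and these give different person-time and different sets of tests. The by-vaccine-type heading does not identify the booster product. The cohort rule protects against other mRNA boosters only by also removing a regimen the Introduction says will be studied.

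**Conclusion.** The point holds as a mismatch between scope and rules. In the TND the written rules class recipients of other boosters as boosted. In the cohort neither reading of the mixed-product exclusion yields the stated scope. This is more than missing detail, because the primary exposure is affected and the text alone cannot settle it.

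The effect on the estimates is unknown. The shifts shown, 0.25 to 0.35 around 0.30 and between-band ratios of 1.12 and 0.91, rest wholly on assumed shares and effects, and vanish if product effects are equal. They show that a distortion is possible, not that it is likely or large. It would also be too strong to say that the planned cross-country comparison is broken: the Introduction promises harmonised analyses only where possible, and a difference in product mix is a risk to them, not a demonstrated failure.

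**What to change.** Before analysis, amend the SAP as follows.

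1. In 3.5, 5.1.1 and 5.1.5, define the analysed exposure as a BNT162b2 booster after two doses of the same primary product (ChAdOx1 or BNT162b2).
2. In the cohort exclusions, limit the mixed-product rule to the first two doses.
3. In the cohort, censor at receipt of any other booster and keep the earlier person-time.
4. In the TND, exclude tests taken after such a booster. Giving other products their own exposure category would also close the gap.
5. Bring the Brazilian population in 3.3 into line with the Introduction.

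The cost is wording and one filter per design, since Tables 1 and 2 list vaccine type, dose and date for both countries. Some boosted person-time and tests are lost, probably mainly in Scotland. The amount cannot be stated, because 3.6 gives no Scottish counts and no split by booster product. These are analysis definitions only and say nothing about which vaccine should be given.
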